Participants will fill in questionnaires (once) to evaluate factors which may impact vascular reactivity [i.e., daily physical activity [International Physical Activity Questionnaire—long version (60)], flavanols-intake [a self-designed questionnaire about the frequency of flavanol-enriched food intake (16, 17, 61)], sleep behavior (Epworth Sleepiness Scale, STOP-BANG), and autonomic function (Autonomic Symptom Profile-COMPASS). We will also assess quality of life and general health status (36-Item Short Form Health Survey, World Health Organization Quality of Life questionnaire-BREF, and only for patients with T2DM Diabetes Quality Of Life questionnaire). In addition to the questionnaires, each participant's physical activity levels (62) and glycemic excursions and variability (63) will be objectively measured during 1 usual week using accelerometry and a Continuous Glucose Monitoring System, respectively.

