#### Additional Outcome Measures

In each participant, physical activity [steps per day and moderate-to-vigorous physical activity (MVPA)] will be evaluated with an accelerometer [Actigraph wGT3X-BT, dominant side, hip (75)] and glycemic excursions (percentages of time in hyper- or hypoglycemic ranges and time in range), risk for hypo- and hyperglycemia (Low and High Blood Glucose Indexes, LBGI and HBGI), and glycemic variability [standard deviation, coefficient of variation, and mean amplitude of glucose excursion (MAGE)] (76) by continuous interstitial glucose measurement (blind mode, IPro2, Medtronic, abdomen) for 1 week, immediately after the second study day. During this week, the above-mentioned restrictions concerning food intake and physical activity are not applicable and participants are encouraged to maintain their normal daily habits. Additionally, participants are asked to fill in a diary concerning their food intake and their physical activities for each day.

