#### Data-Analysis Plan

Effects of CF ingestion on primary and secondary outcome measures will be evaluated within and between groups. Data will be analyzed using a random intercept model in mixed models. Fixed effects will be the group, the supplementation (cocoa flavanols vs. placebo), the time (pre- vs. post-intake of capsules) during each visit for repeated measurements, as well as group × supplementation interaction and time × supplementation interactions. We will also consider the order of both visits in a first intent and this factor will be kept in analyses only if significant. As all groups are matched by age, sex, and BMI, only medication intake, level of physical activity, glycemic excursions, risk for hypo- or hyperglycemia, and glycemic variability will be considered as covariates when analyzing data. In case of drop-outs or missing data, the participant is still included in data analysis providing one out of two visits is completed.

Results will be presented as mean ± standard deviation with its corresponding 95% confidence interval. Level of significance will be set at *p* < 0.05. Data analysis will be conducted using IBM SPSS statistics version 26.

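### The rule that keeps one-visit participants fails in any model carrying the glucose-monitor covariates (or accelerometer activity), because these are measured only after the second study day

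*Protocol article*

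**What the plan says.** Three statements in the protocol article bear on this point.

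- **Retention** (Data-Analysis Plan): "In case of drop-outs or missing data, the participant is still included in data analysis providing one out of two visits is completed". This is the only rule given for missing data.
- **Covariates** (same paragraph): "only medication intake, level of physical activity, glycemic excursions, risk for hypo- or hyperglycemia, and glycemic variability will be considered as covariates when analyzing data". The fixed effects listed just before are group, supplementation, time and two interactions. The model is described as follows: "Data will be analyzed using a random intercept model in mixed models".
- **Timing** (Additional Outcome Measures): the glucose measures are obtained "by continuous interstitial glucose measurement (blind mode, IPro2, Medtronic, abdomen) for 1 week, immediately after the second study day". The accelerometer is worn in the same week.

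The Study Protocol section under Intervention links the covariate terms to these devices: "each participant's physical activity levels (62) and glycemic excursions and variability (63) will be objectively measured during 1 usual week using accelerometry", with a continuous glucose monitor for the glucose measures. That section also lists a long-form physical activity questionnaire, completed once, without saying at which visit.

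**The concern.** A random-intercept model accepts a participant whose second-visit outcomes are missing, which is presumably why the plan can promise to keep one-visit participants. It does not accept a missing covariate in the same way. Under ordinary fitting, a row without a covariate value is dropped. A person-level covariate that was never measured therefore removes every row of that person.

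The glucose covariates do not exist until after the second visit, so the people the retention rule is meant to protect are the ones who cannot have them. The same deletion removes a completer with full FMD and blood pressure data at both visits who declines the wear week or whose device fails. Membership of an adjusted analysis would then depend on a procedure that starts after all FMD and blood pressure measurements are over. Adjusted and unadjusted results would also differ partly because they describe different participants.

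**Working it through.** **Inputs.** Planned group sizes are 15, 10, 30 and 20, total 75 (Eligibility Criteria). No withdrawal or wear-failure rate is given, so 5% to 20% is an assumed range. The stated minimum of nine per group cannot be reproduced, because no standard deviation is given; this point does not rest on it.

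**Step 1: who has what.**

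| Participant | Outcome data | Glucose covariates | Kept by the stated rule | Kept in a model with these covariates |
|---|---|---|---|---|
| Both visits, valid wear week | both visits | yes | yes | yes |
| Both visits, no valid wear week | both visits | no | yes | no |
| Visit 1 only | visit 1 | no | yes | no |

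The last two rows are the conflict. At an assumed 5%, 10% or 20% without wear-week data, 75 × rate = 3.75, 7.5 or 15 participants are affected.

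**Step 2: precision cost when withdrawers are deleted.** Take a random intercept, independent residuals with variance 1, and fixed effects for supplementation, time, their interaction and visit. The post-minus-pre change at one visit has variance 2, and the intercept cancels. The time × supplementation effect is the mean change on cocoa flavanols minus the mean change on placebo:

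Var = 2/n(CF) + 2/n(placebo), where n counts visits with data.

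- 10 completers: 2/10 + 2/10 = 0.400.
- 8 completers + 2 withdrawers, one from each order: 2/9 + 2/9 = 0.444.
- 8 completers, withdrawers deleted: 2/8 + 2/8 = 0.500.
- Ratio 0.500/0.444 = 1.125; √1.125 = 1.061, about 6% in standard error.
- 9 completers + 1 withdrawer: 2/10 + 2/9 = 0.422. Withdrawer deleted: 2/9 + 2/9 = 0.444. Ratio 1.053; √1.053 = 1.026, under 3% in standard error.

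Deleting a completer for want of a wear week costs more, because two visits go. For 2 of 10 the change is from 0.400 to 0.500; √1.25 = 1.118, about 12% in standard error.

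**Step 3: whole-trial check.** In one simulated trial of 75 with 8 visit-1-only participants (assumed residual SD 1.2), the unadjusted model used 75 participants and 284 rows (67 × 4 + 8 × 2). The model with a covariate measured only after visit 2 used 67 participants and 268 rows. The standard error of time × supplementation was 0.285 and 0.293 respectively, a rise of about 3%.

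**Step 4: what the covariate returns.** Each wear-week variable is one value per person, the same at both visits. As a main effect it cancels from the within-person changes. With 10 completers the variance is 0.400 with or without it.

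**The case against.** Several counter-arguments have force.

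- **The covariates are only to be considered.** None is among the listed fixed effects, and a model without them keeps the one-visit participant. This stands. A reader might infer that withdrawers are certain to be lost from the primary FMD analysis; the document does not show that. The loss arises only in models that carry these covariates.
- **Activity has another source.** The questionnaire could supply an activity value, so it is too much to say that activity is measured only after visit 2. It helps a withdrawer only if completed at the first visit, which is not stated. The glucose covariates have no substitute, and they are enough to trigger the deletion.
- **An unseen analysis plan could specify imputation.** It could. But the conflict is between two things stated here, the collection schedule and the retention rule.
- **The timing has a reason.** Diet and exercise restrictions apply before each study day (Guidelines for Participants), and the wear week is placed where they no longer apply, so that usual habits are recorded. This explains the schedule but does not remove its effect on the analysis.
- **The covariates may be useful between groups.** A reader might conclude that adjustment gains nothing at all. That holds only for the within-person contrast in completers. The plan also compares groups, and person-level covariates can change between-group level comparisons.

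A reader might also infer that restoring withdrawers keeps the group with T2DM and no hypertension (n = 10) at the stated minimum of nine. At assumed loss rates of 5%, 10% and 20%, the chance of losing two or more of the 10 is 0.086, 0.264 and 0.624. But 8 completers plus 2 one-visit participants are still fewer than nine completed cross-overs. Dropping the covariate repairs that count only where the loss is a completer's missing wear week.

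**Conclusion.** The point holds in a limited form. As written, the schedule and the retention rule cannot both operate in a model that includes the glucose covariates, or activity taken from the accelerometer. Withdrawers after visit 1 and completers without a valid wear week drop out, and the analysed set changes with the covariates chosen.

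How many people this affects is unknown. In the scenarios above, deleting withdrawers raises the standard error by about 3% to 6%, which is modest; deleting completers costs more per person. The main faults are a stated rule that does not work and analysis sets that differ between models, with most consequence in the small groups (10 with T2DM and no hypertension; 5 per drug class in T2DM with hypertension). The conclusion assumes ordinary mixed-model fitting without covariate imputation. The variance figures also assume independent residuals around a random intercept and, for two withdrawers, one from each order.

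**What to change.** State that the primary FMD model and the main blood pressure model contain no wear-week covariates and include every participant with outcome data from at least one visit. The retention rule then works as written. Use the accelerometer and glucose-monitor variables only in a secondary adjusted analysis of participants who have them, and report its n beside the primary n.

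If an activity covariate is wanted in the main model, the questionnaire can serve only where it was completed at the first visit. Measurements began in October 2018, so its timing cannot be changed for participants already measured.

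The change is to wording only, with no extra participants or procedures, and the within-person contrast in completers loses no precision. The downside is that the wear-week adjustment, including any use in between-group comparisons, becomes secondary.

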This acute, randomized, double-blinded, placebo-controlled cross-over study aims to investigate whether a single intake of a high dose of CF (790 mg flavanols) induces an improvement in endothelial function (primary outcome), a reduction in BP, and an enhancement in muscle vasoreactivity and oxygenation in patients with T2DM compared to healthy controls.

Because hypertension is a common comorbidity in patients with T2DM and as little is known so far concerning possible interferences between antihypertensive drugs and CF actions especially in patients with diabetes mellitus, this study will additionally investigate possible influence of beta-blockers (BB), angiotensin converting enzyme inhibitor (ACEi), or angiotensin receptor blocker (ARB) in diabetic persons with arterial hypertension and non-diabetic persons with essential hypertension treated with these drugs.

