### Participants

#### Eligibility Criteria

All subjects are divided in four groups: (i) patients with T2DM with arterial hypertension (with BB, *n* = 5/ACEi, *n* = 5/ARB, *n* = 5) (*n* = 15), (ii) patients with T2DM without arterial hypertension (*n* = 10), (iii) non-diabetic patients with essential arterial hypertension (BB, *n* = 10/ACEi, *n* = 10/ARB, *n* = 10) (*n* = 30), and (iv) healthy participants (control group; *n* = 20).

Inclusion and exclusion criteria are summarized in Table 2.

**Table 2 T2:** In- and exclusion criteria for participants in this study.

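### FMD is tested within and between four groups at an unadjusted 0.05, and the analysis plan does not tie the stated aim (T2DM compared with healthy controls) to one test

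*Protocol article*

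**What the plan says.** The aims paragraph closing the Introduction makes endothelial function the primary outcome and seeks improvement "in patients with T2DM compared to healthy controls". The next paragraph presents the influence of antihypertensive drug class as an additional question.

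Under Eligibility Criteria, "All subjects are divided in four groups": T2DM with hypertension (n = 15, five per drug class), T2DM without hypertension (n = 10), essential hypertension (n = 30, ten per drug class) and healthy controls (n = 20).

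The Data-Analysis Plan states: "Effects of CF ingestion on primary and secondary outcome measures will be evaluated within and between groups". It specifies one mixed model with fixed effects for group, supplementation and time, "as well as group × supplementation interaction and time × supplementation interactions". The decision criterion is "Level of significance will be set at *p* < 0.05". No term or contrast is marked as the primary test, and no ordering, adjustment or overall gate is given.

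The Power and Sample Size section gives a minimum of nine participants per group. It does not name the comparison that this number serves.

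**The concern.** One primary outcome does not make one primary test. At least three kinds of FMD result could be presented as the answer: a CF effect inside a group, a difference in CF effect between two groups, or an overall interaction. Each is held to the same 0.05. The aim points to T2DM against healthy controls, but T2DM could mean the hypertensive group, the non-hypertensive group, both separately or both combined.

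The article hopes the results may bear on practice guidelines (Discussion) and may serve as a kind of pilot for long-term trials that also looks for non-responders (Introduction). If the contrast is settled only after the results are seen, a chance finding in one group cannot be told apart from the result the trial was built to test.

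**Working it through.** **Inputs from the article.** Four groups of 15, 10, 30 and 20 (Eligibility Criteria); significance level 0.05 (Data-Analysis Plan).

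**Assumptions.** Two-sided tests, since sidedness is not stated. The number of tests is not stated either, so each family below is assumed. Each rate is the chance of at least one significant FMD result when CF has no effect in any group.

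**1. The plan's own figure.** For one pre-named test, 1 − 0.95 = 0.05. The stated level is right if there is a single primary test.

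**2. Four within-group tests.** The groups contain different people, so the tests are essentially independent: 1 − 0.95^4 = 1 − 0.8145 = 0.1855, about 19%.

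**3. Adding the six pairwise between-group tests.** Treating ten tests as independent gives 1 − 0.95^10 = 0.401. That is too high, because the pairwise contrasts are differences of the same four group effects. A null simulation that keeps this correlation (200,000 runs, the article's group sizes, common SD, t-tests on within-participant CF-minus-placebo effects) gives:

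| Family | Pooled variance | Separate variances |
|---|---|---|
| Four within-group | 18.3% | 18.5% |
| Four within-group + one overall group × supplementation test | 18.6% | 19.2% |
| Four within-group + six pairwise | 25.3% | 26.6% |

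The ten-test family therefore runs at about 26%.

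**4. Narrower families.**
- Only the two T2DM-versus-healthy contrasts: they share the healthy group, so their correlation is (1/20) / √[(1/15 + 1/20)(1/10 + 1/20)] = 0.05 / √(0.1167 × 0.15) = 0.38. Under independence the rate would be 1 − 0.95^2 = 0.0975; the simulation gives about 9.3%.
- Only within-group results in the beneficial direction: 1 − 0.975^4 = 1 − 0.9037 = 0.096; the simulation gives 9.5 to 9.7%.

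**5. One named contrast.** Combined T2DM (15 + 10 = 25) against healthy controls (20), tested once: 5%.

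**The case against.** Several objections have force.

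- **A comparison is named.** A reader might infer that the trial has no primary comparison at all. The Introduction does state one in words, T2DM against healthy controls. What is missing is the link from those words to a test, and a definition of T2DM across two groups.
- **No success rule is written.** A reader might infer that significance in any one group would count as success. The article does not say so. A result confined to essential hypertension would not meet the stated aim.
- **Drug-class cells do not belong in the headline.** Adding six class-specific tests (three cells of 5, three of 10) to the ten above takes the simulated rate to about 41%. The arithmetic is sound, but the Introduction calls that question additional, and the Data-Analysis Plan has no within-class test and treats medication only as a covariate.
- **One model need not mean ten tests.** If the between-group question is read from the single interaction term, the rate is about 19%, not 26%.
- **Direction matters.** The aim is improvement, so a significant fall in FMD would not be a positive result. This brings the within-group figure down to about 10%.
- **A separate analysis plan may settle it.** Contrast order and adjustment are often left to such a document, and none is shown. Silence on adjustment alone would not be a point.

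What survives is what the article itself fixes: within-group and between-group evaluation of the primary outcome at one flat level, with the aim attached to neither. Even the narrow readings give about twice the nominal 5%.

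**Conclusion.** The point holds in a limited form. The Data-Analysis Plan leaves open which FMD test answers the stated aim and applies an unadjusted 0.05 to all of them. If any significant FMD result were taken as positive, the false-positive chance would be about 19% (four within-group tests) to 26% (with six pairwise tests). It would be about 9 to 10% if only the two T2DM-versus-healthy contrasts, or only beneficial within-group results, counted.

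These figures rest on assumed families, a global null, equal variances and two-sided tests, except in the beneficial-direction case. They describe what the wording permits. They do not show that the investigators intend to claim success on any one group, and the document does not support a headline of 41%.

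**What to change.** Name in the Data-Analysis Plan one primary FMD contrast that answers the aim, and write it as a model term or a stated combination of terms. One example is the CF-minus-placebo effect in both T2DM groups combined (n = 25) minus the same effect in healthy controls (n = 20), tested at 0.05. Say how the two T2DM groups are weighted, because combining them merges groups that the design separates on purpose.

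If the CF effect within T2DM is also to be confirmatory, put the two tests in a fixed sequence, each at 0.05 and the second tested only if the first succeeds. State the order before unblinding. The aim is comparative, so making the within-T2DM effect the first step would need a reason.

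Report all other within-group, between-group, drug-class and secondary results as estimates with 95% confidence intervals, labelled exploratory.

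The cost is wording only: no added participants or measurements, and no alpha lost on the primary test. The small downside is that the exploratory results cannot be called confirmatory.

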## Discussion

In recent years, there has been an increased attention to polyphenols and their beneficial effects on vascular health. Several studies have been carried out in healthy participants to assess this. However, the studies, acute as well as chronic, on patients with T2DM with a high risk for vascular complications are scarce and show inconsistent results. Possible reasons for this inconsistency might be heterogeneity in the given intervention (dose, duration, source), the studied population (duration of diabetes, severity of comorbidities, BP at baseline, sex), and possibly used medication (vasoactive antihypertensive and antidiabetic drugs). Hence, there is a high need for more acute and chronic research concerning this topic in this population.

This work will provide novel data helpful for the development of strategies in the nutritional education of particularly vulnerable populations, given their high risk for developing cardiovascular disease, including non-pharmacological therapies and strategies that employ lifestyle modification. This intervention might also have implications for the preparation of recommendations in clinical practice guidelines and quality improvement programs aimed at the care of patients with T2DM.

## Ethics Statement

Study procedures were approved by the ethical committee of Ghent University Hospital on April 5th, 2018 (STUDY B670201835660). To enquire all participants and to ensure making an informed decision to participate, each subject will receive an informed consent that first is explained orally by an investigator and thereafter sent by e-mail providing the opportunity to reread this form and to ask questions afterwards. The informed consent contains all details of the research (background, aims, and possible risks or advantageous) and is written in Dutch for good understanding. In case of important protocol modifications, all participants will be informed by e-mail. The results will be submitted to an international peer-reviewed journal and presented at scientific conferences. They will be disseminated through digital science communication platforms, including academic social media, to extend its outreach and usefulness.

## Abbreviations

ACEi: angiotensin converting enzyme inhibitor
ARB: angiotensin receptor blocker
BB: beta-blockers
BP: blood pressure (SBP, systolic blood pressure; DBP, diastolic blood pressure)
CF: cocoa-derived flavanols
dHGE: dynamic handgrip exercise
FMD: flow-mediated dilation
NIRS: Near-infrared spectroscopy
T2DM: type 2 diabetes mellitus.
